## Abstract

**Background:**

Out-of-hospital cardiac arrest (OHCA) is a leading cause of preventable mortality that now affects almost 3,000 people each year in Ireland. Survival is low at 6–7%, compared to a European average of 8%. The Irish Out-of-Hospital Cardiac Registry (OHCAR) prospectively gathers data on all OHCA in Ireland where emergency medical services attempted resuscitation.

The Irish health system has undergone several developments that are relevant to OHCA care in the period 2012–2020. OHCAR data provides a means of exploring temporal trends in OHCA incidence, care, and outcomes over time. It also provides a means of exploring whether system developments were associated with a change in key outcomes.

This research aims to summarise key trends in available OHCAR data from the period 2012 – 2020, to explore and model predictors of bystander CPR, bystander defibrillation, and survival, and to explore the hypothesis that significant system level temporal developments were associated with improvements in these outcomes.

**Methods:**

The following protocol sets out the relevant background and research approach for an observational study that will address the above aims. Key trends in available OHCAR data (2012 – 2020) will be described and evaluated using descriptive summaries and graphical displays. Multivariable logistic regression will be used to model predictors of ‘bystander CPR’, ‘bystander defibrillation’ and ‘survival to hospital discharge’ and to explore the effects (if any) of system level developments in 2015/2016 and the COVID-19 pandemic (2020) on these outcomes.

**Discussion:**

The findings of this research will be used to understand temporal trends in the care processes and outcomes for OHCA in Ireland over the period 2012-2020. The results can further be used to optimise future health system developments for OHCA in both Ireland and internationally.

## Introduction

### Out-of-Hospital Cardiac Arrest

Out-of-hospital cardiac arrest (OHCA) describes the sudden loss of mechanical function of the heart and the absence of blood flow around the body, occurring outside of a hospital setting
^
1,
2
^. OHCA is the most time-critical medical emergency, with survival depending on the prompt actions of the community where OHCA occurs, emergency medical services (EMS) and in turn, appropriate follow-on hospital care
^
3
^. Internationally, the annual incidence of OHCA treated by emergency medical services (EMS) is estimated to be 30 – 97 individuals per 100,000 population, median age ranges from 64 to 79 years and more than half of victims are male
^
4
^. OHCA with attempted resuscitation has an incidence of 56 per 100,000 population per year in Europe and is considered the third leading cause of death
^
5
^. Survival to/ immediately after hospital discharge ranges from three to twenty percent internationally and is eight percent in Europe
^
6
^. Of those that do survive to discharge in Europe and North America, approximately seventy percent are still alive at three years
^
7
^. In Ireland there are now almost 3,000 OHCAs with attempted resuscitation each year of which six to seven percent involve survival to hospital discharge
^
8
^.

### The Chain of Survival

The ‘chain of survival’ describes the critical actions that can link an OHCA victim with survival
^
9
^. This chain involves early access to care, early cardiopulmonary resuscitation (CPR), early defibrillation and post resuscitation care
^
10
^. CPR and defibrillation are exquisitely time sensitive interventions and thus health systems face a significant challenge in ensuring OHCA patients have timely access to these treatments
^
11
^. Thankfully, the simplicity, affordability and increasing awareness of these interventions mean that they can be cascaded to the community and performed by ‘bystanders’ when cardiac arrest occurs
^
12
^. Thus, at population level these represent the most important OHCA interventions
^
13,
14
^. In circumstances where bystanders have not initiated CPR, dispatch assisted CPR (where the EMS emergency call taker provides CPR instruction to bystanders over the phone) can further improve survival following OHCA
^
15
^. 

CPR and defibrillation exist alongside several other OHCA interventions that can be delivered in the community and enroute to hospital by EMS. Randomised controlled trials have demonstrated that delivery of medications such as adrenaline and amiodarone may have additional benefits for some patient groups, while trials of airway management and mechanical CPR devices have failed to show significant survival improvements
^
16–
19
^. An additional novel but resource intense hospital (or hospital outreach) treatment ‘eCPR’ (extracorporeal cardiopulmonary resuscitation) uses a mechanical device to temporarily replace heart and lung function. eCPR has shown significant promise in specific OHCA sub-populations
^
20
^. However, the degree to which this treatment can be made available in an equitable fashion at population level is yet uncertain
^
21,
22
^. In terms of follow on in-hospital care, international guidelines now recommend that OHCA patients are cared for in specialist cardiac arrest centres, while acknowledging limited evidence for this recommendation outside of specific patient subgroups
^
22,
23
^.

### Out of Hospital Cardiac Arrest & Quality Improvement Registries

The science underpinning the ‘chain of survival’ is unquestionably of critical importance in OHCA care. However, scientific research alone will not be sufficient to improve OHCA outcomes and must be accompanied by a focus on real world implementation and quality improvement
^
24
^. To this end the European Resuscitation Council recommend that ‘health systems should have population-based registries which monitor the incidence, case-mix, treatment and outcomes for cardiac arrest’ and that these data ‘should inform health system planning and responses to cardiac arrest’
^
25
^.

An internationally agreed ‘Utstein’ registry dataset has been devised which facilitates national and international comparison of OHCA
^
26
^. A recent pan European survey reported that six countries (including Ireland) had an OHCA registry with full population coverage, fourteen had partial population coverage and seven countries reported not having an OHCA registry
^
27
^. Comprehensive data on the Irish experience of OHCA is provided by the Irish Out-of-Hospital Cardiac Arrest Registry (OHCAR). OHCAR achieved national coverage using the Utstein dataset in 2012, and by 2020 this contains over 20,000 cases. In terms of the period considered in this study OHCAR does not include OHCA with EMS response but without attempted resuscitation. We anticipate that approximately fifty percent of cases recorded in OHCAR are witnessed (European average 66%), and twenty percent have an initial ‘shockable rhythm’ (European average 20%)
^
6
^. The primary sources of OHCAR data are patient care records and dispatch data from Ireland’s statutory ambulance services. OHCAR has provided invaluable continuous quality improvement data on an annual basis to ambulance services. To date however, no temporal analyses have been conducted to assess the impact of national interventions on survival in Ireland. Nor has the database been interrogated to determine whether international trends in OHCA (including increased bystander CPR and associated survival improvements
^
28–
30
^) are mirrored in the Irish data.

### Emergency medical services in Ireland

Ireland’s population is now in excess of five million people, for whom emergency medical services (EMS) are provided by the National Ambulance Service (NAS)
^
31
^. In Ireland’s capital Dublin, Dublin Fire Brigade (DFB) are contracted to provide an emergency ambulance service alongside the NAS. Each year these services respond to in excess of 300,000 ambulance calls
^
32
^. The National Emergency Operations Centre (NEOC) coordinates statutory emergency service responses to OHCA for most of the Irish state. In the Dublin metropolitan area EMS response is coordinated by both NEOC and the DFB east regional communications centre (ERCC). EMS care across the Irish state is provided by Paramedics or Advanced Paramedics who number approximately 2,500 & 700 respectively
^
33
^. All front-line ambulances must be staffed by at least a paramedic grade practitioner. A small number of EMS physicians supplement this care on a voluntary as available basis; however, they are not a core component of the statutory response.

Paramedic and Advanced paramedic scope of practice is determined by a statutory agency, the Pre-Hospital Emergency Care Council (PHECC). PHECC publish clinical practice guidelines and maintain a practitioner register
^
34
^. Only Advanced Paramedics are permitted to provide intravascular medications or to perform endotracheal intubation. Mechanical CPR devices are now widely available on all frontline ambulances. eCPR is generally not available in Ireland. In addition to statutory EMS providers, Ireland also has an extensive network of voluntary community first responders (CFRs) who can be dispatched by NEOC to OHCA to provide early CPR and defibrillation
^
35,
36
^.

### OHCA Health System Developments in Ireland 2012–2020

Over the period 2012–2020 that OHCAR has been in existence, Ireland has undergone several health system developments that are pertinent to OHCA care.
Figure 1 summarises a timeline of these developments. The Pre-Hospital Emergency Care Council national Citizen CPR or Call-Check-Compress programme was launched in 2010
^
37
^. This public awareness campaign involved a series of national roadshows combined with a major national television, cinema, on-line and transport advertising designed to increase bystander CPR. Then in 2012 the NAS launched their ‘one life’ quality improvement programme
^
38
^. This ongoing programme focuses on several key aspects of OHCA including community interaction and public education, NEOC call taking and dispatch, EMS quality care on scene, and finally quality data management and audit processes. In 2014 the Irish Health Information and Quality Authority (HIQA) published a health technology assessment of public access defibrillation in Ireland
^
39
^. This was commissioned by government to inform decision making around proposed legislation to mandate public defibrillator availability. The health technology assessment estimated the clinical and cost effectiveness of a range of potential Irish public access defibrillation configurations, ranging from comprehensive to targeted
^
39
^. It estimated that between two and ten additional OHCA survivors could be achieved annually; however, none of the models achieved the threshold for cost effectiveness. It advised that targeted AED deployment in higher incidence locations in combination with an EMS-linked AED register and increased public awareness could potentially render the programmes’ cost effective
^
39
^. Ultimately the proposed legislation was abandoned, and a comprehensive national EMS-linked AED register is yet to be established.

**Figure 1. f1:**
[figure not shown]
OHCA Health System Developments in Ireland 2012–2020. NAS: National Ambulance Service, QI: Quality Improvement, PAD: Public Access Defibrillation, CPR: Cardiopulmonary Resuscitation, CFR: Community First Responder, GP: General Practitioner, OHCA: Out-of-Hospital Cardiac Arrest.

 In 2015 and 2016 the National Ambulance Service transitioned from a system of multiple regional independent control centres to a single national control centre (NEOC). This significant change allowed an enhanced level of resource co-ordination and further allowed dispatch assisted CPR to be fully embedded as a standard of care at national level. Between 2016 and 2020 the Irish Heart Foundation ‘CPR 4 schools’ programme trained 1,827 teachers in 531 schools to perform CPR training for a potential 288,197 students. Between 2016 and 2020 lay community first responder groups increased from 100 to 175 nationally. In 2017 the NAS created four new Community Engagement Officer posts to support CFR activities and expansion. Also between 2016 and 2020 GP (general practitioner) first responder numbers doubled to almost 200 individuals
^
40
^. The final year of this study period 2020 is exceptional in that it represented the first year of the Covid-19 pandemic, the first wave of which occurred between February and July 2020
^
41
^. The Irish health service responded by introducing a range of public health measures including travel restrictions, schools and business closure, cessation of large indoor gatherings, and other social distancing measures
^
42
^. In terms of OHCA, internationally Covid-19 is known to have detrimentally affected systems of care and was associated with prolonged EMS response and worse short-term outcomes including survival compared to pre-pandemic periods
^
43
^. The effects of COVID-19 on OHCA in Ireland have not yet been systematically evaluated; however similar trends are probably likely. Thus, it is necessary to consider this as a significant OHCA development in the 2020 period.

### Focus of this study

This study will examine data from the Irish Out-of-Hospital Cardiac Arrest Registry (OHCAR) to describe OHCA incidence and its care processes in Ireland over the period 2012 to 2020. We will further interrogate this data to identify key OHCAR variables that predict key outcomes. We anticipate approximately 18,000 relevant observations will be available for analysis. We will consider survival to hospital discharge, bystander CPR, and bystander defibrillation to be key outcomes of interest over the study period. We hypothesise that of the timeline of OHCA developments described above, two key developments are likely to be associated with a significant change in outcomes. Given the scale of reorganisation and centralisation of EMS control in 2015 and 2016 on the backdrop of the ongoing NAS ‘one life’ project we hypothesise that the NAS transition from a system of multiple regional independent control centres to the single national control centre (NEOC) would be associated with improvements in bystander CPR and survival to hospital discharge. In turn, given Covid-19’s detrimental effect on OHCA internationally we hypothesise that COVID-19 would be associated with significant reductions in bystander CPR, bystander defibrillation and survival to hospital discharge in Ireland.

### Study aims

The study will have four aims.

●To summarise key trends in available OHCAR data from the period 2012 – 2020●To harness available OHCAR data to explore and model predictors of ‘bystander CPR’, ‘bystander defibrillation’ and ‘survival to hospital discharge’●To explore the hypothesis that significant system level developments in 2015 & 2016 (the National Ambulance Service transition to a single national control centre) were associated with a temporal improvement in the above outcomes●To explore the effect of COVID-19 on the above outcomes.

## Methods

### Study design

Key trends in available OHCAR data from the period 2012 – 2020 will be described and evaluated using descriptive summaries and graphical displays. Multivariable logistic regression will be used to model predictors of ‘bystander CPR’, ‘bystander defibrillation’ and ‘survival to hospital discharge’ and to explore the effects (if any) of system level developments in 2015/2016 and the COVID-19 pandemic on these outcomes. The R software for statistical computing will be used for analysing the data.

### Study population, setting and time frame

The population for this study will be patients of all ages who suffered un-witnessed, or bystander witnessed OHCA during the time period 2012 – 2020 and are included in the Irish national OHCAR cardiac arrest registry database. Patients who had an EMS witnessed OHCA will be specifically excluded from this current study. Follow on work will consider this distinct excluded group separately.

### Variables and categories of concern

All analysis will be based on the variables shown in
Table 1. Variables 1–19 will be obtained from the OHCAR. Variables 20, 21 and 22 represent component time periods that are a priori considered to be potentially significant in the context of either system level developments or key population health challenges (Covid-19) during the study time period. Variables 20,21 and 22 will be dummy variables created using the ‘Year’ variable. Variables 20 and 21 will be linked dummy variables derived from the same 3-level categorical indicator of period and will be simultaneously included in regression models. We do not expect collinearity of these predictors, as transition and post-transition period correspond to years 2015 and 2016, and 2017 through 2020, respectively. The Covid period dummy variable (variable 22) will be an indicator of 2020 only, and thus should allow us to estimate any shift in survival in the final year of the study data.
Table 1 highlights the independent variables that will be explored for each outcome of interest. Where an original OHCAR variable has multiple potential associated categories, we will collapse these categories to avoid decreased statistical power from analysis of an excessive number of potentially sparse categories. Original and collapsed categories are shown in
Table 1. Season will represent the ‘winter’ healthcare period (October to March) as compared to other as ‘winter’ is a period of increased demand for the Irish healthcare service. The three time categories chosen are adopted based on previous OHCA research
^
44
^. Home (versus other) location was chosen as home represents the most common location for OHCA in Ireland. ‘Year’ (variable 9) will be treated as a continuous variable to conserve degrees of freedom and statistical power.

**Table 1. T1:** Variables for analysis.

Variable Number	Variable	Categories	Collapsed Categories	Outcome of Interest		
				Bystander CPR	Bystander Defibrillation	Survival to Hospital Discharge
**1**	**Airway** ** Management**	**Basic ** **Management**	**None of the listed devices ** **used, OPA/NPA, No advanced** ** airway**			*****

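### The year-based Covid flag counts pre-pandemic January 2020 as exposed, and the year-based transition flags also cover cases not dispatched by the merged control centre

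*Protocol article*

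**What the plan says.** Methods, Variables and categories of concern, states that variables 20, 21 and 22 "will be dummy variables created using the" Year variable. The Covid dummy "will be an indicator of 2020 only, and thus should allow us to estimate any shift in survival in the final year" of the data. For the other two, "transition and post-transition period correspond to years 2015 and 2016, and 2017 through 2020, respectively". The same section limits all analysis to the variables of Table 1. That table has Season (October to March against the rest) and Urban or Rural, but no control centre, service or region.

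Two background sections bear on these definitions.

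- OHCA Health System Developments in Ireland 2012–2020 calls 2020 the first pandemic year, "the first wave of which occurred between February and July 2020". It describes the 2015–2016 change as the National Ambulance Service (NAS) merging its own regional control centres into one, NEOC.
- Emergency medical services in Ireland says that NEOC "coordinates statutory emergency service responses to OHCA for most of the Irish state", and that coordination in metropolitan Dublin is shared between NEOC and the fire-brigade centre, ERCC.

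**The concern.** Study aims 3 and 4 concern the control-centre transition and Covid-19, and the protocol states a direction for each. Both estimates depend on who is coded as exposed.

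A flag built from Year cannot separate January 2020 from the months after it. Nor can it separate cases handled by the merged NAS centre from cases handled by ERCC. If unexposed cases sit in the exposed group, the coefficient averages the effect with zero and moves toward the null. For Covid, the protocol's own dates show that this happens. For the transition, the protocol shows that the flag is broader than the change it stands for, but not by how much.

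**Working it through.** The protocol gives no effect size or power calculation, so there is no stated figure to reproduce.

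**Inputs from the protocol.** About 18,000 observations over nine years (Focus of this study); survival of 6–7%, taken as 6.5% (Introduction); first wave from February 2020.

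**Assumptions.** Even case load, so 18,000/9 = 2,000 a year; no secular trend; no Covid effect in January; all effect sizes; a 60% bystander CPR rate.

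**1. Covid flag.** January's share is 31/366 = 8.5%, or about 170 of 2,000 cases. Only 2020 carries the flag, so the Covid term reproduces the 2020 mixture. With baseline risk p0 and risk p1 under Covid:

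p(2020) = 0.0847 × p0 + 0.9153 × p1

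For survival with a true OR of 0.70:

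- Baseline odds: 0.065/0.935 = 0.0695.
- Covid odds: 0.0695 × 0.70 = 0.0487, so p1 = 0.0464.
- Mixture: 0.0847 × 0.065 + 0.9153 × 0.0464 = 0.0480, with odds 0.0504.
- Estimated OR: 0.0504/0.0695 = 0.725.
- Shrinkage of the log OR: 1 − ln(0.725)/ln(0.70) = 9.8%.

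| Outcome | True OR | OR with year flag | Log-OR shrinkage | Power, year flag | Power, flag from February |
|---|---|---|---|---|---|
| Survival, 6.5% | 0.60 | 0.633 | 10.5% | 86% | 92% |
| Survival, 6.5% | 0.70 | 0.725 | 9.8% | 60% | 68% |
| Survival, 6.5% | 0.80 | 0.817 | 9.3% | 30% | 35% |
| Survival, 6.5% | 0.90 | 0.908 | 8.8% | 10% | 12% |
| Bystander CPR, 60% | 0.80 | 0.815 | 8.4% | 86% | 91% |

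Power is two-sided at 5%, from a logistic model with Year, transition, post-transition and Covid terms only. The flag from February recovers the true OR in each row.

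**2. Splitting 2020.** Survivors in the year: 2,000 × 0.065 = 130. February–July: 130 × 182/366 = 65. August–December: 130 × 153/366 = 54. A two-level Covid term for survival would rest on few events.

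**3. Transition flags.** The protocol does not give the ERCC share, d. As an illustration only, suppose that ERCC cases were wholly unexposed and that the true survival OR is 1.30. The same mixture formula with d in place of 0.0847 gives:

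| ERCC share (assumed) | OR with year flags | Log-OR shrinkage |
|---|---|---|
| 5% | 1.285 | 4% |
| 10% | 1.269 | 9% |
| 20% | 1.239 | 18% |
| 30% | 1.209 | 28% |

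Partial exposure of ERCC would reduce every figure in the last column.

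**4. Precision of a contrast by centre.** Under the same assumptions, the standard error of the post-transition log OR from a period × centre interaction is 0.317 at d = 5%, 0.230 at 10% and 0.172 at 20%. The year-only model gives about 0.215. The contrast is less precise at the two smaller shares and more precise only at the larger one.

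**The case against.** On Covid, the protocol openly defines variable 22 as a final-year shift and calls 2020 the first pandemic year; February to July dates only the first wave. One month in twelve moves the estimate little, and a finer split spends events that the plan wants to conserve. It stands that this is a disclosed, coarse definition with a small effect. But aim 4 is the effect of COVID-19, and leaving January out needs no extra parameter. A reader might infer a larger error by starting the pandemic in March; the protocol gives no such date.

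On the transition, the case against is stronger. A reader might infer that ERCC cases are an unexposed control group that the plan throws away. The documents do not support that:

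- Dublin is coordinated by both centres, dispatch-assisted CPR is described as embedded nationally, and nothing says that ERCC practice stayed unchanged.
- Dispatch data are named as a primary registry source, but no dispatching-centre field is stated to exist.
- A difference-in-differences would remove only changes common to both services. By the protocol's account, community first responders are dispatched by NEOC, and the 2017 engagement posts and the 'one life' programme belong to NAS. Their effects would still be credited to centralisation.
- Urban or Rural cannot adjust for Dublin against other urban areas.

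The transition aim is also phrased as a system-level development, so a national average is a legitimate estimand. The Discussion already concedes that other factors may drive any association.

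**Conclusion.** The Covid part holds and is minor. By the protocol's own dates, about 8.5% of the flagged period precedes the pandemic, and the Covid log OR shrinks by roughly 8 to 10%. At survival ORs of 0.60 to 0.80 this costs 5 to 8 points of power. These figures rest on an even case load, no January effect and no secular trend.

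The transition part holds only as a limit on interpretation. Variables 20 and 21 apply to all cases from 2015 on, while the merger concerned NAS centres that do not serve the whole state. The shrinkage of 4 to 28% rests on an assumed ERCC share of 5 to 30% and on wholly unexposed ERCC cases; the documents support neither. A reader might also infer that the post-transition OR is biased toward zero overall. That is not shown: the same term absorbs schools CPR training and first-responder growth from 2016 to 2020, which could push it the other way.

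**What to change.** 1. Derive variable 22 from incident month: 1 from February 2020 onward, 0 otherwise, so that January 2020 is unflagged. Season is split by month, so month must be known at registry level, and the registry can supply the flag before anonymisation. The cost is one derived field. Show first wave against later 2020 only as a secondary description, because survivors are few.

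2. Ask whether the registry records dispatching centre or service. If it does, add a sensitivity analysis of the period effect, either restricted to NEOC cases (with NAS regional-centre cases as their counterpart before the merger) or with a period × centre interaction. Report it beside the overall OR and not as a clean difference-in-differences. The cost is one requested field and one further model, with lower precision if the ERCC share is small.

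3. If it does not, state that the post-transition OR is a national average that includes cases not coordinated by NEOC. The cost is one sentence.

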		**Not Covid Period**				

### Statistical model building and interpretation procedures

For each outcome we will build a logistic model: initially a full model with all relevant predictors will be fitted. A refined model will then be built using a stepwise model selection procedure (STEPAIC function in R). This procedure builds several models from all possible combinations of the predictors by sequentially adding and dropping predictors and finally selects the model with the lowest AIC. The stepwise model will then be further improved by examining addition of pairwise interaction variables and retaining any interactions which improve fit. We will evaluate each model (full, stepwise and with interactions) based on AIC. In addition, the model deviance and a Hosmer-Lemeshow Goodness of Fit (GOF) test will be inspected for each model. To assess linearity between continuous predictors and the log odds of the outcome we will rely on good model fit as indicated by the Hosmer-Lemeshow goodness of fit test. We will also use logistic regression with higher order terms (polynomial terms) to explore if the relationship between the outcome and the continuous predictors is indeed non-linear. If higher-order terms are significant, these will be retained in the model, otherwise they will be dropped from the model. We will also attempt to ameliorate fit by including pair-wise interaction terms between predictors. We will summarise the effect of each individual variable in the final model using odds ratios and 95% confidence intervals. The effect of any significant interactions in the final model will be explored graphically. After selecting the final model from the three models, we will evaluate the predictive ability of the final best fitting model using 10-fold cross-validation and evaluate the prediction accuracy for the model.

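### The no-collinearity statement covers only the two period terms against each other; continuous Year in the same model gives the post-transition term a VIF near 14 and about three times the standard error

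*Protocol article*

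**What the plan says.** All points are in the Protocol article, Methods.

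- **Variables and categories of concern.** The transition (2015–2016), post-transition (2017–2020) and Covid indicators "will be dummy variables created using the" Year variable. The first two "will be simultaneously included in regression models", and the only remark on collinearity follows directly: "We do not expect collinearity of these predictors, as transition and post-transition period correspond to years 2015 and 2016, and 2017 through 2020, respectively". On the third: "The Covid period dummy variable (variable 22) will be an indicator of 2020 only". Year itself "will be treated as a continuous variable to conserve degrees of freedom and statistical power".
- **Table 1.** Year and all three indicators are marked for bystander CPR, bystander defibrillation and survival to discharge.
- **Statistical model building and interpretation procedures.** For each outcome "initially a full model with all relevant predictors will be fitted". Stepwise AIC selection follows. Polynomial terms are then explored for continuous predictors: "If higher-order terms are significant, these will be retained in the model, otherwise they will be dropped from the model". No degree is set, and Year is not exempted.

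**The concern.** The full model holds Year and three step functions of Year. With the intercept, that is five time parameters on nine distinct calendar values. The collinearity remark looks only at whether the two periods overlap, and not at the variable they are built from. The correlation between Year and the post-transition indicator is 0.87.

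The post-transition coefficient is the direct test of aim 3, and the Covid coefficient is the test of aim 4. If the post-transition term can be estimated only imprecisely, 18,000 records promise more than the model delivers, and an odds ratio close to 1 with a wide interval says little. The plan also leaves the time terms open to two data-driven steps, polynomial retention and AIC selection. Either can change the precision of a period coefficient or the quantity it estimates.

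**Working it through.** The article states no VIF, standard error or power figure, so there is none of its own to reproduce.

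**Inputs**
- About 18,000 observations (Focus of this study) over nine years. An equal split of 2,000 per year is an assumption.
- Survival of 6–7% (Introduction); 6.5% is used.
- T = 1 in 2015–2016, P = 1 in 2017–2020, C = 1 in 2020, reference 2012–2014; Year linear.
- Other covariates are assumed unrelated to year.

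**Formulas**
- VIF = 1/(1 − R²), with R² from regressing one time term on the others. This equals total over residual sum of squares.
- SE(log OR) = 1/√[2,000 × p(1 − p) × residual sum of squares].
- Detectable OR at 80% power = exp(2.80 × SE).

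**1. The pair alone.** With only T and P in the model, each has a VIF of 1.30. The plan's remark is right for this pair.

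**2. Adding linear Year.** Over the nine years the total sum of squares of P is 2.222. Its residual sum of squares is 1.500 given T and C, and 0.1607 given T, C and Year.
- VIF of P: 2.222/1.500 = 1.48 without Year; 2.222/0.1607 = 13.83 with it.
- 2,000 × 0.065 × 0.935 = 121.55.
- SE of P without Year: 1/√(121.55 × 1.500) = 0.074. Detectable OR 1.23.
- SE of P with Year: 1/√(121.55 × 0.1607) = 0.226. Detectable OR 1.88.
- Ratio of standard errors: √(13.83/1.48) = 3.06.

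From 6.5% survival, an OR of 1.88 means about 11.6% (odds 0.0695 × 1.88 = 0.1307; 0.1307/1.1307).

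**3. All terms, and polynomial Year**

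| Time terms | VIF T | VIF P | VIF C | SE P | SE C | Detectable OR, P |
|---|---|---|---|---|---|---|
| T, P, C | 1.30 | 1.48 | 1.19 | 0.074 | 0.105 | 1.23 |
| + Year | 3.46 | 13.83 | 1.98 | 0.226 | 0.135 | 1.88 |
| + Year² | 4.14 | 13.83 | 3.53 | 0.226 | 0.181 | 1.88 |
| + Year³ | 7.61 | 33.66 | 8.08 | 0.353 | 0.274 | 2.69 |

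A quadratic leaves the post-transition term where it was and costs precision in the Covid term. Only a cubic makes the post-transition term worse.

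**4. Sensitivity to the assumptions.** With yearly counts rising linearly from 1,600 to 2,400, the VIF of P is 14.36. Other growth patterns gave 14.3–14.4 and a standard-error ratio of 3.01–3.04. At 6% survival the with-Year detectable OR is 1.93 (SE = 1/√(112.8 × 0.1607) = 0.235); at 7% it is 1.84 (1/√(130.2 × 0.1607) = 0.219). For bystander CPR at an assumed 70%, the detectable OR goes from 1.12 without Year to 1.41 with it.

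**5. Power by simulation.** 300 runs used a true post-transition OR of 1.3, half that log-odds effect in the transition years, 6.5% survival and no secular trend. Power for the post-transition term was 93% without Year and 18% with linear Year. A Year-only model had a lower AIC than the period-only model in 59% of runs, although the true pattern was a step.

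**6. Gradual effects.** An effect growing evenly from zero in 2014 to full size in a given year was projected by least squares onto T, P, C and Year. The share appearing in P is 72% if complete by 2016, 81% by 2017, 50% by 2018 and 24% by 2019. Year takes up part of the remainder. The ramp shapes are assumptions; the article gives none.

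**The case against.** The strongest reply is that the wider standard error is the proper price of adjusting for drift. The Introduction cites international trends of rising bystander CPR and survival, and describes Irish programmes begun before 2015. If Year is omitted, a pure trend of b per year on the log-odds scale with no transition effect puts 5b into the post-transition term and 2b into the Covid term. A trend OR of 1.05 per year would then show as a spurious post-transition OR of 1.05⁵ = 1.28. The with-Year and without-Year coefficients therefore estimate different things, and 1.23 is not a precision target that the with-Year model could reach. This stands, and it is why Year should stay in the model.

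Four stronger readings are tempting but not supported:
- *The collinearity sentence is false.* In context it refers to the two period dummies, and for them it is correct. Its fault is what it leaves out.
- *The polynomial rule necessarily worsens the post-transition term.* A quadratic does not. The rule can do so only if a cubic or higher term is tried and found significant.
- *The plan will read a null as no improvement.* The article says nothing of the kind. It speaks of exploring effects, reports 95% confidence intervals and acknowledges confounding in the Discussion.
- *Gradual effects largely vanish into Year.* That depends on when the effect is assumed complete. The control-centre change is placed in 2015 and 2016, and for completion by 2016 or 2017 most of the effect remains in the post-transition term.

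The VIFs also describe the full model and any selected model that keeps Year with the period terms. They need not describe a model from which AIC has removed one of them.

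**Conclusion.** The concern holds in a limited form. The plan's only statement on collinearity overlooks the one collinearity that matters for aim 3. In the full model the post-transition term has a VIF of about 14 and a standard error about three times that of the model without Year. For survival, the detectable odds ratio is about 1.88. The transition and Covid terms are affected less (VIF 3.5 and 2.0).

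This is imprecision, not bias, and it is no reason to drop Year. What the plan fixes badly is the treatment of the time terms: Year is open to polynomial terms of unstated degree, and both Year and the dummies are open to AIC selection. The meaning and precision of the aim 3 and 4 estimates are therefore not settled in advance. The figures rest on equal or steadily rising yearly counts, 6–7% survival, and other covariates unrelated to year.

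**What to change.** 1. Limit the collinearity sentence to variables 20 and 21 against each other. Add that both, and variable 22, are collinear with Year, and give the VIFs and the resulting detectable odds ratios.
2. For aims 3 and 4, force linear Year and variables 20–22 into the model together, exempt from stepwise AIC and from the significance-based polynomial rule.
3. Report the period contrasts with Year (departure from a linear trend) as the test of aim 3. Report those without Year as a companion, labelled as total change confounded with secular trend.
4. State that a confidence interval including 1 in the with-Year model is not evidence of no effect.
5. Add a slope-change fit as a sensitivity analysis for effects that accrue gradually.

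The cost is wording and a few extra fits on the same data. The stated precision becomes less favourable. The loss of precision itself remains, because Year stays in the model, but readers will see it.
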